### 3.3. Participants

To participate in the 3WP, a patient must be: 1) a critically ill adult in the ICU and 2) have a high risk of dying during the hospitalization as judged by the ICU physician, or a decision has been made to withdraw or withhold life support in anticipation of death. Family member(s) and/or the person listed as the patient’s designated decision maker (hereafter referred as family) can be included in wish solicitation and fulfillment. Based on our prior experience, we anticipate less than 10% of patients will be able to express their wishes due to critical illness [28,46]. Eligibility identification and wish solicitation and fulfillment are performed by any clinician, typically the ICU nurse and confirmed with the ICU physician(s). The 3WP is not meant to substitute a goals of care conversation, and as such, the nurse who wants to implement 3WP would confirm with the ICU physician that the patient is an appropriate candidate, and that the family is aware of their poor prognosis.

Regardless of whether the patient participates in the 3WP, families of all patients who die in the ICU will be contacted to complete an after-death survey. “Families” are those who are listed as the emergency contact or next of kin in the patient’s medical record, must be ≥ 18years old, and English- or Spanish-speaking. We anticipate that contact information will be missing for 5–10% of patients (i.e., due to homelessness). Additionally, families (10 per site) of patients who participated in the 3WP will also be invited for semi-structured interviews. All nurses (approximately 250 nurses across 3 ICUs) who work in the ICU in which the 3WP is being implemented will be eligible to complete surveys regarding burnout and compassion before and after 3WP implementation. Ten nurses at each site who have implemented the 3WP for their patients will also be invited to semi-structured interviews.

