### 3.6. Outcomes and analysis

#### 3.6.1. Patient/family outcomes.

The primary outcome is changes in the Emotional and Spiritual Support factor on the family reported BFS after 3WP implementation. Three BFS-derived measures will be analyzed: Respectful Care and Communication (5 questions, Cronbach α = 0.82), Emotional and Spiritual Support (3 questions, Cronbach α = 0.77), and the BFS-Performance Measure (BFS-PM). The Respectful Care and Communication factor score sums 5 items about staff behavior: (1) listened to concerns; (2) provided medical treatment patient wanted; (3) were kind, caring, and respectful; (4) kept family members informed about patient’s condition and treatment; and (5) attended to personal care needs. The Emotional and Spiritual Support (ESS) factor score sums 3 items about whether staff provided: (1) enough emotional support before death; (2) enough spiritual support; and (3) enough emotional support after death. Based on our prior work [31], we hypothesize that the 3WP will increase the ESS factor score. The BFS-PM, a single item asking for a global rating of EOL care, will be a secondary outcome. Secondary outcomes will also include scores on the HADS (depression and anxiety) and PCL-5 (PTSD) measures.

**Statistical analysis**. We will use an analysis approach that accounts for the stepped-wedge design of this study [66,67]. We will use mixed effects logistic and linear mixed effects models to assess the effect of the intervention on the BFS ESS factor score, BFS-PM, FS-ICU, HADS, and PCL-5. These models adjust for center effect and the confounding effects of time and 3WP implementation. With $Y_{ijt}$ as the quantitative outcome for patient i from center j at time t, the model for patient/family reported outcomes is:

$Y_{ijt}=\mu +\alpha_{j}{\;+\;\beta }_{t}+X_{ijt}\theta +\;Z_{ijt}\varphi +\in_{ijt},$

where μ is the intercept, $\gamma_{i}$ is a random center effect,

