$\beta_{t}$ is the fixed time effect, $X_{ijt}$ is the indicator of treatment mode for subject i cluster j at month t, θ represents the 3WP implementation effect, $Z_{ijt}$ are pre-specified patient and practice level covariates and $\in_{ijt}$ is random errors. We will also approximate the secular time trend $\beta_{t}$ linearly in time with βt. This model will accommodate unobserved center effects. All analyses will be carried out based on the intention to treat principle, which means that the treatment mode variable ($X_{ijt})$ is determined by the scheduled initiation of implementation based on randomization, but not by individual patient/family enrollment in the 3WP. Covariates, including age, sex, race/ethnicity, language, insurance status, and utilization of life-support measures, will be included in the model. We will also perform “as-treated” analyses to compare patients before implementation and patients who received 3WP after implementation and those who did not. Subgroup analyses will evaluate how outcomes are affected by race, ethnicity, and sex as a biological variable.

**Power calculations.** The primary outcome is the family-reported ESS factor score on the BFS, and the secondary endpoints include BFS-PM, FS-ICU, HADS and PCL-5. Across the 3 SNH ICUs, we estimate that 375 (90%) deaths per year will qualify for after-death surveys About 40% of families will return the survey based on our prior work [58,59]. With approximately 100 surveys returned before and 275 surveys after 3WP implementation and a 2-sided significance (α) level of 0.05, we will have 89.3% power to demonstrate the difference in the BFS ESS factor based on our preliminary data [59].

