## 4. Discussion

This manuscript describes a protocol to implement and evaluate the 3WP, a low cost, high value palliative care intervention in 3 low-resourced hospitals. The study will be performed across 3 SNHs in the Los Angeles County healthcare system, the second largest municipal health system in the nation, and thus will provide valuable insight for implementing palliative care interventions in culturally diverse populations and safety-net settings. The intervention is low risk and there are minimal safety concerns. As a hybrid effectiveness-implementation study that utilizes mixed methods [74], our study will provide rich perspectives by integrating both quantitative and qualitative evaluations.

Our study is not without limitations. First, neither patients nor clinicians are randomized; however, this study will provide an assessment of effectiveness and implementation under real-world conditions. Participation in a randomized trial would require explicit patient and/or family member consent, which would generate confusion for dying patients and their family members about compassionate end-of-life interventions that are determined by randomization. Delayed and declined engagement would likely decrease the sample size and result in a biased patient sample. Second, because 3WP is an initiative that is dependent on nurses to voluntarily offer to their patients, it is also dependent on staffing radios and how busy the ICU is. SNHs may have more limited time and effort to devote to eliciting and implementing wishes for dying patients, although our prior experience has shown that clinicians value the ability to provide this type of enhanced care to their patients and families [28]. We will perform additionally perform an as-treated analysis, but also iteratively assess the best strategies for overcoming SNH limitations throughout the study. Third, three clusters may seem small, but this is an acceptable number of clusters for the stepped-wedge design [45,75]. Fourth, we are anticipating a survey return rate of approximately 40% from families of deceased patients. Although seemingly low, this is typical of after-death surveys and consistent with our experience and prior studies.[25,60,61,76]

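### The as-treated comparison of recipients with non-recipients is confounded by the voluntary, workload-dependent offering the protocol describes, and can show an effect of 3WP when there is none

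*Protocol article*

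**What the plan says.** The main analysis in section 3.6.1 is by intention to treat: the treatment variable "is determined by the scheduled initiation of implementation based on randomization, but not by individual patient/family enrollment in the 3WP". The same paragraph adds as-treated "analyses to compare patients before implementation and patients who received 3WP after implementation and those who did not".

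The protocol also describes how receipt comes about. Section 3.3 says that "the nurse who wants to implement 3WP would confirm with the ICU physician that the patient is an appropriate candidate", and that the family should already know the prognosis is poor. The Discussion lists a limitation "because 3WP is an initiative that is dependent on nurses to voluntarily offer to their patients", and continues that "it is also dependent on staffing radios and how busy the ICU is". Within that limitation it then states: "We will perform additionally perform an as-treated analysis". It does not warn that this analysis is confounded.

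On adjustment, section 3.6.1 says: "Covariates, including age, sex, race/ethnicity, language, insurance status, and utilization of life-support measures, will be included in the model". Section 3.5.1 abstracts further variables, among them expected death, family presence at death, family meetings and palliative care consultation, but section 3.6.1 does not name these as covariates. Neither section names a measure of staffing or workload.

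**The concern.** The primary outcome, the Emotional and Spiritual Support (ESS) score, asks families whether staff gave "1) enough emotional support before death; (2) enough spiritual support; and (3) enough emotional support after death". A nurse with time to offer wishes plausibly also has time to give support that families rate well, with or without 3WP. A patient whose death is foreseen and whose family is present and informed is also more likely to be offered 3WP. Families of all ICU decedents are surveyed, so the non-recipients include deaths on busy shifts and deaths that nobody foresaw. The contrast therefore mixes any effect of the wishes with the circumstances that led to the offer.

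The stake is interpretation. If ITT comes out diluted or imprecise, an as-treated result with a small p-value would be the obvious figure to cite as the effect of receiving 3WP, and as planned it could not carry that meaning.

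**Working it through.** **Inputs from the protocol article.** Section 3.6.1 gives about 100 surveys before and 275 after implementation, two-sided alpha 0.05 and power 89.3%. The counts agree with its other figures: 375 × 0.40 = 150 surveys a year, and 150 × 2.5 years (section 3.1) = 375. Control periods of 6, 8 and 10 months (Abstract: 6–10 months, staggered by 2) with three ICUs of equal size give (150/36) × 24 = 100 before launch.

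**Assumptions, not in the document.** Reach p = 50% (range 30–70%). Selection s = 0.3 SD (range 0.2–0.4): families of would-be recipients rate ESS higher by s even without 3WP.

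**Step 1: the plan's own figure.** The difference and SD behind 89.3% are not stated, so the figure can only be inverted. For two independent means, d = (1.960 + 1.243) × √(1/100 + 1/275) = 3.203 × 0.1168 = 0.374 SD. This serves as a yardstick.

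**Step 2: bias when the true effect is zero.** Set the mean of would-be non-recipients at 0 and of would-be recipients at s. Everyone before launch averages p·s.
- Recipients v non-recipients: s = 0.30 SD, or 0.30/0.374 = 80% of the yardstick.
- Recipients v pre-implementation: s − p·s = (1 − p)s = 0.15 SD, or 40%.
- All post- v all pre-implementation (ITT): p·s − p·s = 0.

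**Step 3: false positives.** Recipients v non-recipients at 50% reach is 137.5 v 137.5 surveys. SE = √(2/137.5) = 0.1206, and 0.30/0.1206 = 2.49, so P(p < 0.05) ≈ Φ(2.49 − 1.96) ≈ 70%. Over the assumed ranges this runs from 33% (s = 0.2, reach 30% or 70%) to 91% (s = 0.4, reach 50%). Simulation with 375 surveys, 3 ICUs, 30 months, centre effects and linear or monthly time gives +0.30 SD with 65–72% rejections v non-recipients, and about +0.15 SD with 8–12% v pre-implementation patients.

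**Step 4: a different selection mechanism.** Here an unmeasured staff-time factor drives both the offer (logistic slope b) and ESS (correlation r). The true effect is zero and receipt about 50%.

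| r | b | v non-recipients (SD; rejections) | v pre-implementation (SD; rejections) |
|---|---|---|---|
| 0.3 | 1 | +0.25; 54% | +0.11; 9% |
| 0.2 | 1 | +0.17; 29% | +0.08; 8% |
| 0.2 | 0.5 | +0.09; 11% | +0.04; 5% |
| 0 | 1 | 0.00; 6% | −0.01; 5% |
| 0.3 | 0 | 0.00; 5% | 0.00; 5% |
| −0.3 | 1 | −0.24; 52% | −0.12; 9% |

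ITT is centred on zero with 4–5% rejections in all these rows.

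**Step 5: a complier-average estimate.** This is the ITT effect divided by reach, or two-stage least squares (2SLS) with scheduled launch as the instrument for receipt. Nobody receives 3WP before launch, so the randomised date can serve as an instrument. With a true recipient effect of 0.5 SD under the step 2 assumptions it centres on 0.49–0.50, against 0.65 (v pre-implementation) and 0.80 (v non-recipients) as-treated.

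It has two limits.
- Precision: the SE is about 0.37 SD with linear time and 0.70 SD with monthly time, so 95% half-widths are 1.96 × 0.37 = 0.73 and 1.96 × 0.70 = 1.37 SD. Power against 0.5 SD is about 30% and 11%.
- Exclusion restriction: if launch raises everyone's ESS by 0.2 SD and receipt adds nothing, the expected estimate is 0.2/0.5 = 0.40 SD (simulated 0.39).

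**The case against.** Four points can be made for the plan.

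1. **The bias is conditional.** No section quantifies a link between receipt and ESS apart from the wishes, or gives its sign. If nurses offer 3WP chiefly to the most distressed families, the contrast would show harm; if either link is absent, there is no bias. This stands. A reader might infer that the as-treated analysis will show a benefit where none exists. The documents support only that it can show a spurious effect, with benefit the more natural direction.
2. **The analysis is supplementary.** ITT by randomised schedule governs, the Discussion pairs the as-treated analysis with ongoing work on delivery, and nothing calls it the effect of receiving 3WP. The first contrast named, against pre-implementation patients, is the less biased one. This stands and limits the severity.
3. **The covariate list is open.** It is introduced by a word that allows additions, the model refers to pre-specified patient and practice level covariates, and section 3.5.1 abstracts expected death and family presence. This stands in part. Those variables could enter the model, but the protocol's own stated driver, workload, has no named measure.
4. **A complier estimate should not take over.** A reader might infer that 2SLS removes the problem and should replace the as-treated analysis. The document does not support that. Section 3.1 calls 3WP a unit-level intervention, expects contamination under patient-level randomisation and trains the ICU nurses, so an effect on families without wishes is plausible. The estimate is essentially ITT rescaled and cannot rescue an imprecise ITT result. This stands.

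**Conclusion.** The point holds in limited form. By the protocol's own account of delivery, the recipient versus non-recipient contrast is confounded, and no named covariate captures the stated cause. Under the assumed 0.3 SD selection and 50% reach, a null intervention would show about +0.30 SD against non-recipients, with roughly two chances in three of p < 0.05. Against pre-implementation patients the bias is half as large and the rejection rate only modestly above nominal. These sizes rest on assumed selection and reach; weaker selection shrinks them and opposite selection reverses them. The primary ITT conclusion is unaffected. This is an inexpensive improvement to a supportive analysis, not a flaw in the main one.

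**What to change.** - Keep ITT by the randomised schedule as the only inferential effect estimate.
- Report recipient and non-recipient results after launch as descriptive or exploratory, without p-values, and say that receipt depended on staffing, workload and clinician judgement.
- If an as-treated model is kept, adjust for variables already abstracted under section 3.5.1: expected death, family presence, family meetings and palliative care consultation. State that workload remains unadjusted.
- Beside the ITT result, add a complier-average estimate with its interval: 2SLS in the same centre-and-time model, with scheduled launch as the instrument for receipt. State its likely imprecision (SE about 0.4–0.7 SD with 375 surveys at 50% reach) and its assumption that launch does not affect families who receive no 3WP, which is doubtful for a unit-level programme.

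The cost is a few sentences in the analysis plan and a few lines of code. Section 3.6.4 already has nurses document 3WP in the health record, so no new data are needed. What is given up is a p-value for receipt that could not be interpreted causally.

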### 3.2. Setting

The 3 SNHs in this study are part of the Los Angeles County Department of Health Services (DHS), which is the second largest municipal health system in the nation and provides care to patients regardless of their ability to pay. Over 50% of patients do not speak English and about 10% are unhoused. The patient population is 55–80% LatinX, 20% Asian, and 10% black, with many living individuals below the federal poverty level. Although all 3 hospitals serve poor, under- or uninsured, and non-English-speaking patients, they are of different sizes, have different geographical catchment areas, and patient populations. Because the mortality is the highest in medical ICU’s, this is where we will implement and evaluate the 3WP in these 3 Los Angeles DHS SNHs. Of note, hospital 1 only has one combined medical-surgical ICU.

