### 3.5. Data collection

#### 3.5.1. Electronic health record (EHR) abstraction.

Each decedent will be characterized using EHR data, including the patient’s age, sex, race/ethnicity, language, insurance status, co-morbidities, and ICU and hospital length of stay. We will also note palliative care consultations, utilization of life-sustaining treatments (mechanical ventilation, vasopressors, or dialysis), and the occurrence of CPR as these factors have been shown to be associated with quality of death [51–53]. We will manually abstract occurrence of family meetings, reason for ICU admission, resuscitation status at the time death, whether the family was present at the time of death, and whether the death was expected. Expected death is defined as any physician documentation during the terminal hospitalization that the patient was terminal, had a grave prognosis, was receiving hospice care, had imminently life-threatening disease in the context of a poor prognosis, or was dying; this information was previously reliably abstracted from the medical record (reabstraction κ=0.67; 91% agreement) [54]. Double abstraction will be performed for 30 patients and a kappa will be calculated to evaluate inter-rater reliability, with appropriate changes in abstraction process or abstractor training implemented to increase inter-rater reliability if needed.

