#### 3.6.4. Implementation outcomes.

The Reach, Effectiveness, Adoption, Implementation, and Maintenance (RE-AIM) framework will be used to define implementation outcomes (Table 2). *Reach:* Each month, we will obtain lists of deaths in each ICU from the bioinformatics department. This will be the denominator to determine the proportion of eligible patients who received the 3WP. Nurses will be asked to document a 3WP note in the EHR, such that we will be able to record who initiated and implemented the initiative and track the number of clinicians involved at each SNH. *Effectiveness:* The effectiveness of the 3WP in improving the EOL experience for patients/families and nurses will be evaluated by surveys and interviews (above). *Adoption.* We will compare variation in rates of 3WP patient enrollment and proportion of clinician participation across the 3 SNHs. *Implementation.* Nurses’ answers to the 4 questions on fidelity to core functions will be averaged and compared across SNHs. We will also describe categories of wishes, number of wishes, and percent of elicited wishes implemented and by whom. We will present the average cost per patient, and the number and proportion of no-cost wishes. These descriptive statistics will be compared across centers and with historical multi-center data [46]. *Maintenance.* We will trend the descriptive statistics (patients enrolled, clinicians involved, wishes implemented, cost of wishes), by month and by center. After 2.5 years, we will conclude survey collection and remove the research assistant who was available to assist with wish implementation but continue to provide monetary resources to purchase items for patients/families for an additional 12-month period. This period will represent the maintenance period and will also provide an estimation of 3WP cost when there is no on-site research assistant should the site choose to continue the intervention; these data will be provided back to 3WP leaders.

**Table 2 pone.0320843.t002:** Application of the RE-AIM framework to mixed method evaluation of 3WP implementation.

Domain	Existing knowledge gaps in 3WP implementation	Quantitative data	Qualitative data

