Reach	Extent to which clinicians are willing to uptake 3WP as ICU initiative in SNHs Extent to which under-served patients and families are willing to accept 3W offering	% of ICU nurses involved in 3WP implementation % of eligible patients who are offered and receive 3WP Characteristics of patients who participated (demographics, insurance, clinical characteristics)	Identify factors influencing 3WP acceptability for families Identify factors influencing 3WP feasibility for nurses
Effectiveness	3WP feasibility and effectiveness has not been evaluated in SNHs Quantitative evidence of improved EOL experiences & clinician burnout Whether patient population SNHs will favorably respond to 3WP Whether 3WP has an effect on family psychological symptoms	Effect of 3WP on family’s perspective of EOL care (BFS) Effect of 3WP on family’s anxiety, depression, and PTSD Effect of 3WP on nurse burnout	Explore effect of 3WP on family’s EOL experience, satisfaction, bereavement, and psychological symptoms Explore effect of 3WP on clinician burnout, agency, stress of work
Adoption	3WP adoption as part of EOL care in SNHs unknown	% of eligible patients who receive 3WP as part of EOL care compared across the three SNHs	Ascertain how 3WP is integrated into workflow at each SNH, perceived benefits and burdens
Implementation	The extent of 3WP implementation fidelity (adherence to core functions) in SNHs is unknown; unclear if fidelity will vary across centers Unknown how categories of wishes, # of wishes/patient, cost compare to prior data	Rankings of fidelity to core functions (nurse surveys) Categories of wishes, # of wishes, when implemented, by whom, and cost/patient	Assessment of the forms (and adaptations) used to achieve core functions via nurse and leadership interviews Assessment of families’ and clinicians’ experience of 3WP
Maintenance	Extent to which 3WP becomes embedded into ongoing EOL care in SNHs is unknown	Variation in 3WP implementation over time Continuation of 3WP beyond the study period that included surveys and research assistant	Obtain clinician’s opinions on what influence 3WP maintenance Explore the factors that influence sustainability after removal of research assistant

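### Reach counts all ICU deaths as eligible patients, and the as-treated comparison sets recipients against patients who could not have qualified for 3WP

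*Protocol article*

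**What the plan says.** **Who can receive 3WP.** Under section 3.3 of the protocol article a patient must "have a high risk of dying during the hospitalization as judged by the ICU physician", or there must be a decision to limit life support in expectation of death. The nurse also confirms with the physician that the patient is suitable and that the family knows the outlook.

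**Who is surveyed.** The survey population is wider, because "families of all patients who die in the ICU will be contacted to complete an after-death survey", whether or not the patient took part.

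**Reach and Adoption.** Section 3.6.4 says that each month "we will obtain lists of deaths in each ICU from the bioinformatics department", and then: "This will be the denominator to determine the proportion of eligible patients who received the 3WP". Table 2 words the Reach measure as the percentage "of eligible patients who are offered and receive 3WP". It words Adoption as a percentage of eligible patients compared across the three hospitals.

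**As-treated analysis.** Section 3.6.1 makes the analysis by scheduled rollout the main one. It adds as-treated analyses that "compare patients before implementation and patients who received 3WP after implementation and those who did not". No eligibility restriction is stated. The covariates named are age, sex, race/ethnicity, language, insurance and use of life support; the list is introduced as non-exhaustive.

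**What is abstracted.** Section 3.5.1 records "whether the family was present at the time of death, and whether the death was expected", together with resuscitation status at death. Expected death rests on a physician's note at any point in the final admission. The reliability cited from earlier work is kappa 0.67 with 91% agreement.

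**Setting.** Section 3.2 says the hospitals differ in size and patient population, and that "hospital 1 only has one combined medical-surgical ICU".

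**The concern.** An ICU death list includes sudden deaths in patients who never met the rule in section 3.3. Counting them as eligible contradicts that rule and lowers Reach for a reason unrelated to whether staff offered 3WP. If the share of such deaths differs between hospitals, a comparison on the same denominator would show a gap in uptake that is partly case mix. In a type 2 hybrid study the implementation results are a main product, so their labels matter.

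The as-treated comparison has a related problem. Recipients had to qualify. Pre-implementation patients and post-implementation non-recipients are drawn from all ICU decedents. If families of expected and unexpected deaths rate support differently, the groups would differ even if 3WP had no effect. The Discussion offers this analysis as a response to voluntary, workload-dependent delivery, so it is likely to be read as the effect of receiving 3WP.

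**Working it through.** **1. The plan's own figures (section 3.6.1).** Surveys per year: 375 × 0.40 = 150, so 375 over 2.5 years. With 6, 8 and 10 control months at three hospitals of equal volume: 150/12/3 × 24 = 100 before, leaving 275 after. This matches the plan. The 89.3% power cannot be reproduced because no effect size or SD is given. In a simple two-sample comparison at two-sided 0.05 it corresponds to d = (1.960 + 1.243) × √(1/100 + 1/275) = 0.374 SD, which serves below only as a yardstick.

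**2. Share of ICU deaths that met the rule (f).** This is not stated, so I assume 0.60–0.90. The cited reliability gives a rough anchor for documented expected death. Chance agreement is pe = (0.91 − 0.67)/(1 − 0.67) = 0.727. With equal rater marginals, p² + (1 − p)² = 0.727 gives p = 0.84. The mirror root, 0.16, is algebraically possible, and the figure describes the cited sample, not these hospitals.

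**3. Reach.** Counting only recipients who died in the ICU, Reach on all deaths = f × Reach among eligible decedents.

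**4. As-treated, before implementation v recipients.** Let δ be the ESS gap, in SD, between expected and unexpected deaths. Its size and sign are assumed. The difference due to composition alone = (1 − f) × δ.

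| f | Reach on all deaths if 40 / 60 / 80% among eligible | Composition difference (SD) at δ = 0.2 / 0.5 / 0.8 |
|---|---|---|
| 0.60 | 24 / 36 / 48% | 0.08 / 0.20 / 0.32 |
| 0.84 | 33 / 50 / 67% | 0.03 / 0.08 / 0.13 |
| 0.90 | 36 / 54 / 72% | 0.02 / 0.05 / 0.08 |

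Two hospitals with the same 60% uptake but f of 0.60 and 0.90 would show 36% and 54%, an 18-point gap. At δ = 0.5 the composition difference is 0.08/0.374 = 22% of the yardstick at f = 0.84, and 0.20/0.374 = 53% at f = 0.60.

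**5. As-treated, recipients v post-implementation non-recipients.** With Reach r among eligible decedents, the unexpected share of non-recipients = (1 − f)/(1 − r × f). At f = 0.837 and r = 0.60 this is 0.163/0.498 = 33%, a composition difference of 0.33 × 0.5 = 0.16 SD at δ = 0.5.

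**6. Precision cost of restricting.** At f = 0.837 and r = 0.60, restriction leaves 100 × 0.837 = 84 before and 275 × 0.837 × 0.60 = 138 recipients. Two-sample power at d = 0.374 is 77%, against 81% with all 100 pre-implementation surveys.

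**The case against.** The strongest reply has four parts.

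- **The as-treated analysis is supplementary.** It sits in a condensed article with an open covariate list that already includes life-support use, and the full plan may settle the population. This lowers the weight of that half. It does not touch the Reach sentence, which mislabels its denominator as written.
- **All ICU deaths is an objective count.** Documented expected death would bring in charting differences between hospitals. This stands, and is the reason to report both denominators rather than replace one with the other.
- **The sizes are assumed.** Neither f nor δ is in the documents. This stands too. The 18-point gap and the 53% figure come from the unfavourable end of the range.
- **Adoption has no stated denominator of its own.** The text speaks of enrolment rates and Table 2 of eligible patients. The concern about Adoption is therefore conditional on reuse of the death list.

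A reader might also infer more than the documents support:

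- *That the expected-death field would remove the bias.* It would not. Any physician note in the final admission is not the same as the judgement in section 3.3. Nurses choose whom to approach, families may decline, and this selection remains among expected deaths. The field is also described only for decedents.
- *That the as-treated result must favour 3WP.* That needs families of expected deaths to give higher ratings, and no figure on this is given.
- *That recipients who leave the ICU alive or die elsewhere are counted in the Reach numerator.* The text does not say so; it leaves the numerator open.
- *That the primary analysis is biased.* Exposure there follows the randomised schedule, and unexpected deaths fall in both phases. They dilute the effect but do not create this bias.

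**Conclusion.** The point holds in a limited form. The Reach denominator contradicts the plan's own eligibility rule, and Reach among eligible decedents is understated by the factor f: 60% reads as 36–54% for f of 0.60–0.90, and as about 50% at the 84% back-solved from the cited reliability. Adoption inherits this if it uses the same list and f differs by hospital. The combined medical-surgical ICU makes that plausible but does not show it.

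The as-treated groups differ in eligibility by design, and no named covariate captures whether the death was expected. With δ = 0.5 SD the composition difference between pre-implementation patients and recipients is 0.05–0.20 SD over the same range of f, before any covariate adjustment. Its sign is that of δ, which is unknown. The correction is worth making because it is cheap. It concerns the implementation measures and a supplementary analysis, not the intention-to-treat primary result.

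**What to change.** **Reach and Adoption.** Report both on two denominators: all ICU deaths, labelled as such and not as eligible patients, and ICU decedents with documented expected death. Count only recipients within each set, and list separately any recipients who did not die in the ICU.

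**As-treated analysis.** Restrict all three groups to documented expected deaths, or adjust for that field. Label the analysis exploratory and state that confounding from nurse selection and family refusal remains. Do not adjust for family presence or resuscitation status at death except as a sensitivity analysis: both are recorded at the end of the stay and 3WP may affect them.

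**Cost.** Only the analysis wording changes, since the field is already abstracted for decedents. Restriction costs a few points of power (about 77% against 81% in the example above). The main drawback is that expected death is an imperfect proxy for eligibility (cited kappa 0.67), and its documentation may rise once 3WP prompts talk about prognosis. Show the share of expected deaths by period and by hospital so that readers can see any such shift.
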